#### Treatment outcomes analyses

2.8.2

Primary outcomes comprise the CAPS-5 PTSD severity and TLFB percent days of substance use. PTSD-related cognitions and substance use craving will be examined as potential outcome mediators of intervention effects on the primary outcomes, the remaining follow-up measures discussed above comprise secondary outcomes. Generalized linear mixed models (GLMMs) will be used to model treatment outcomes with the form of GLMM chosen to well-model the respective outcome. The models will include fixed effects for follow-up time, treatment condition, and their interaction together with random intercepts for participants. We expect outcomes to vary by gender, age, race/ethnicity, and baseline PTSD severity so the models will include these as additional fixed effects. Missing data will be addressed using multiple imputation by chained regressions within intervention arms. Wald tests will assess whether there is an interaction between treatment condition and time of follow-up using results aggregated over models fit to the imputed datasets; if there is no such interaction, a Wald test will assess whether there is a main effect for treatment condition.

Secondary exploratory analyses will assess gender as a potential moderator of treatment effects as work has suggested women may show greater treatment gains in trauma-focused therapies compared to men and women have higher rates of developing PTSD prior to an SUD compared to men [27,60]. The potential mediating roles of changes in PTSD-related cognitions and substance use craving on treatment outcomes will be investigated and we will investigate whether changes in PTSD symptomology mediate subsequent changes in substance use outcomes. We will implement multiple analyses to investigate these potential mediation pathways. For each follow-up, we will fit generalized linear models (GLM) for the mediators and outcomes to implement the potential outcomes causal mediation analyses described by Imai et al. [61] These analyses will generate estimates of average direct and average causal mediation effects of the intervention on the outcomes. Alternate longitudinal causal mediation analyses, particularly those examining time-lagged effects of changes in PTSD symptomatology on subsequent SUD outcomes, will develop and employ marginal structural models.

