Sample size was determined using Monte Carlo simulation considering uniform 30% dropout over time, correlations between outcomes across time of .30, a group standardized effect for PTSD symptoms and days substance use of .58 (Cohen's d) based on our previous research, and a .05 significance level. A sample size of 168 subjects provides >80% power to identify between group effects under these conditions.

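### The primary analysis tests the treatment-by-time interaction first and the treatment effect only if there is none, so no single test decides efficacy for either primary outcome

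*Protocol article*

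**What the plan says.** The rule is in the protocol article, section 2.8.2 (Treatment outcomes analyses), and applies to the two primary outcomes named there, CAPS-5 severity and TLFB percent days of substance use.

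- Model: a generalized linear mixed model with "fixed effects for follow-up time, treatment condition, and their interaction together with random intercepts for participants".
- Covariates: "We expect outcomes to vary by gender, age, race/ethnicity, and baseline PTSD severity so the models will include these as additional fixed effects".
- First test: "Wald tests will assess whether there is an interaction between treatment condition and time of follow-up".
- Second test, conditional on the first: "if there is no such interaction, a Wald test will assess whether there is a main effect for treatment condition".

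The only significance level in the article is in the sample-size paragraph of the same section: "a .05 significance level". It is not divided between the two tests. That paragraph also assumes "a group standardized effect for PTSD symptoms and days substance use of .58" and "correlations between outcomes across time of .30", with 30% dropout spread evenly over time, and concludes: "A sample size of 168 subjects provides >80% power to identify between group effects under these conditions". It does not say which of the two tests the power refers to.

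**The concern.** The trial asks whether adding M-PE gives better outcomes than TAU. The model speaks of follow-up time and carries baseline PTSD severity as a covariate. Time therefore most naturally means the four post-randomisation visits in section 2.3: end of treatment and 1, 3 and 6 months after. On that reading the interaction asks whether the arm difference changes between visits. With time as categories, the test has 3 degrees of freedom and no direction. It can be significant when M-PE is better, when it is worse, or when the sign changes.

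The test that does address the question, the treatment main effect, is reached only if the first test is negative. Two things are at stake:

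- **Error rate.** If a significant interaction is reported as evidence of a treatment effect, each primary outcome has two chances at .05.
- **Decision.** If a significant interaction is not such evidence, the rule reaches it and stops, with no between-arm comparison named in the article.

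The text does not choose between these readings, so the choice could be made after the results are known. An effect that varies over time is plausible here. End of treatment falls about 6 weeks after randomisation (section 2.3), while residential stays run about 30 to 90 days (section 2.2.1). Substance use may therefore be held down in both arms at the first follow-up.

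**Working it through.** **Inputs from the article.** 168 participants with equal allocation (section 2.2), so 84 per arm; four follow-ups (section 2.3); correlation .30, dropout 30%, d = .58, level .05 (section 2.8.2).

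**Assumptions added here.** Two-sided tests; time coded as four categories; normal outcomes with SD 1; monotone dropout; available-data generalised least squares in place of multiple imputation. The article does not fix the dropout schedule by visit, so two were used, with retention of .925, .85, .775, .70 or of 1, .90, .80, .70. Ranges below span the two.

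**1. The plan's own power figure.** At one time point, completers per arm are 84 × 0.70 = 58.8. Power = Φ(0.58 × √(58.8/2) − 1.96) = Φ(3.145 − 1.96) = Φ(1.185) = 88.2%. The statement of more than 80% is met.

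**2. Type I error of the two-stage rule, no effect at any visit.**

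- Either rejection counts: 1 − 0.95 × 0.95 = 9.75%, which is 1.95 times .05. Simulation with the inputs above (20,000 runs) gives 10.0–10.1%. It gives 9.3% if the main effect is coded as the arm difference at the first visit.
- Only the main effect counts: 0.95 × 0.05 = 4.75% (simulated 4.8–4.9%).

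**3. How often the rule stops at the interaction.** Let δ be the vector of four arm differences, V its covariance matrix, and C the three contrasts of later visits with the first. Interaction power is P(χ²₃(λ) > 7.81), with λ = (Cδ)ᵀ(CVCᵀ)⁻¹(Cδ). For the average over visits, power is Φ(δ̄/SE − 1.96), with SE = 0.115 or 0.112 under the two schedules.

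| Effect at the four follow-ups | λ | Interaction significant | δ̄ | Power of averaged contrast |
|---|---|---|---|---|
| .58 throughout | 0 | 5% | .58 | 99.9% |
| .145, .29, .435, .58 (or the reverse) | 4.9–5.0 | 43–44% | .3625 | 88–90% |
| 0, .193, .387, .58 | 8.7–9.0 | 70–71% | .29 | 71–73% |
| 0, .58, .58, .58 | 13.0–13.8 | 87–89% | .435 | 96–97% |

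Simulation of the first three patterns agrees (interaction 4.8%, 43% and 70%); a separate simulation of the fourth gave 85.7%.

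**4. One unconditional test.** A single contrast at .05 has type I error of 5% (simulated 5.2% for the average over visits).

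**The case against.** The strongest objections, and what stands of each:

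- **The article does not say that a significant interaction counts as efficacy.** Correct. A reader might infer that the plan doubles its false-positive rate. That follows only if either rejection is read as a treatment effect; if only the main effect counts, the error is 4.75%. The inflation must be stated conditionally. What stands is that the text leaves the reading open.
- **Visit-specific differences can be taken from the fitted model, and a full protocol or SAP may specify them.** This also stands, so it cannot be said that the trial has no such comparison. But the conditional order of tests is stated in the article itself, and it makes the direct test of the treatment difference depend on another result.
- **Under the plan's own single effect of .58 the harm is small.** True if the effect is constant: the main effect is then tested in about 95% of trials. A reader might infer that the rule will usually stop at the interaction when benefit builds up. For growth from .145 to .58 it stops in only 43–44%; the high figures need an effect that starts at zero, and the article gives no trajectory.
- **A figure of 18.5% across both primary outcomes is tempting** (1 − 0.95⁴). It treats CAPS-5 and TLFB as independent, which the article does not claim, and brings in the separate matter of having two primary outcomes. It is not relied on.
- **If baseline were a level of time, the interaction would itself be the efficacy test.** The reference to follow-up time and the baseline PTSD covariate speak against this, most clearly for CAPS-5.

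**Conclusion.** The point holds in this form. Section 2.8.2 fixes a two-stage rule with no allocation of the significance level and does not say which test decides efficacy. Type I error per primary outcome is about 9.75% if either stage may decide and about 4.75% if only the main effect may. In the second case the deciding test is withheld in about 5% of trials under a constant .58, 43–44% under gradual growth from .145, and 87–89% if the effect is absent at end of treatment and .58 afterwards.

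The 9.75% and 4.75% need only two tests at .05 that are close to independent. The stopping rates rest on the assumptions listed with the calculation, chiefly categorical post-randomisation time and normal outcomes; percent days of use may well be modelled otherwise. The sample-size statement is not in error. It holds for a direct between-arm contrast, which this rule does not guarantee will be run.

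**What to change.** For each primary outcome, pre-specify one M-PE minus TAU contrast, for example the difference averaged over the four follow-ups, estimated from the model that keeps the interaction. Test it at .05 whatever the interaction shows. Delete the clause that makes the treatment test conditional. Report the interaction test and the visit-specific differences with confidence intervals as supportive, and tie the power statement to the named contrast.

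The average is one valid choice. A single-visit contrast also works (88.2% power with 58.8 completers per arm), as does a joint 4-df test of any arm difference (simulated type I error 5.4%, power 99.0% at a constant .58), though the joint test has no direction.

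The cost is analysis-plan wording only: no participants and no data. Recruitment is ongoing, so the change can be made before results are known. The downside of averaging is dilution when the effect is present at only some visits. Power is about 71–73% for linear growth from 0 to .58, and about 25% if .58 appears only at the last visit. If a late effect is the main expectation, the contrast should be chosen with that in mind.

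### The GLM mediation estimate for craving on substance use allows no treatment-affected confounder, yet the plan's own hypotheses make post-randomisation PTSD symptoms a candidate for one

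*Protocol article*

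**What the plan says.** All the relevant text is in section 2.8.2 (Treatment outcomes analyses) of the protocol article.

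- Mediators: "PTSD-related cognitions and substance use craving will be examined as potential outcome mediators of intervention effects on the primary outcomes". The primary outcomes are CAPS-5 severity and TLFB percent days of use, so craving is a mediator of the effect on use.
- A further hypothesis: "we will investigate whether changes in PTSD symptomology mediate subsequent changes in substance use outcomes".
- Method and estimands: "For each follow-up, we will fit generalized linear models (GLM) for the mediators and outcomes to implement the potential outcomes causal mediation analyses", and "These analyses will generate estimates of average direct and average causal mediation effects of the intervention on the outcomes".
- A second method: "Alternate longitudinal causal mediation analyses, particularly those examining time-lagged effects of changes in PTSD symptomatology on subsequent SUD outcomes" are to use marginal structural models. The wording gives the PTSD-to-use path priority. It neither assigns these models to craving nor excludes craving from them.
- Planned effect, from the sample-size paragraph: "group standardized effect for PTSD symptoms and days substance use of .58".

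The covariates named for the main outcome models are gender, age, race/ethnicity and baseline PTSD severity, all fixed before randomisation. Covariates for the mediation models are not listed.

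**The concern.** A split into average direct and average causal mediation effects, from a mediator model and an outcome model, needs more than randomised treatment. No variable that treatment changes may be a cause of both mediator and outcome. If there is one, the mediator's coefficient in the outcome model absorbs part of that variable's effect. The correct time order of mediator and outcome does not cure this.

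For craving and substance use, the plan supplies two of the three links itself: treatment changes PTSD symptoms, and PTSD change may affect later use. The third link, from PTSD symptoms to craving, is not stated, but nothing in the article rules it out and the causal reading of the craving estimate requires its absence.

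Mediation is a declared aim in the Introduction, and the Discussion says that the mediator and moderator results are meant to help tailor treatment. Craving could be reported as a mechanism, and so as a treatment target, when it only tracks PTSD symptoms.

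**Working it through.** **The plan's own figure first.** Section 2.8.2 claims more than 80% power with 168 participants, d = .58, 30% dropout and a .05 level (two-sided assumed here). For one follow-up, n per arm = 84 × 0.7 = 58.8 and SE = √(2/58.8) = .184. Then .58/.184 = 3.145, 3.145 − 1.96 = 1.185, and power is 0.88. The claim is met. It concerns the between-group effect; no figure is given for mediation.

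**Model for the check.** Let A be treatment, L post-randomisation PTSD, M craving and Y use, each with within-arm SD 1:

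- L = −.58A + error (.58 is the plan's figure)
- M = gL + error (g is assumed)
- Y = bL + 0·M + error (b is assumed; craving has no effect on use)

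The two GLMs are M on A, and Y on A and M. In linear models without an A-by-M interaction, the mediation effect is a product of coefficients:

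- A in the mediator model: −.58g
- M in the outcome model, with L omitted: bg
- False indirect effect: −.58 × g² × b, against a true value of 0

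If all of the effect on use runs through PTSD, the total effect is −.58b and the false share is g², the squared PTSD-craving correlation. If the total effect on use is instead the plan's .58, the extra part is a direct effect of A. Both models contain A, so the false indirect effect is unchanged and only the denominator changes.

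| g | b | False indirect effect (SD, absolute) | Total effect .58b | Share of .58b | Share of .58 |
|---|---|---|---|---|---|
| .3 | .3 | .58 × .09 × .3 = .0157 | .174 | 9% | 2.7% |
| .5 | .3 | .58 × .25 × .3 = .0435 | .174 | 25% | 7.5% |
| .5 | .5 | .58 × .25 × .5 = .0725 | .290 | 25% | 12.5% |
| .6 | .5 | .58 × .36 × .5 = .1044 | .290 | 36% | 18% |
| 0 | any | 0 | | 0% | 0% |

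**Do baseline covariates cure it?** Mostly not. Baseline PTSD was added to both models, correlated .30 with later PTSD (the plan's own value: "correlations between outcomes across time of .30"), with two million simulated participants. For g = .3 the false share of the total effect through PTSD was 8%. For g = b = .5 it was 23%. If M-PE also lowers craving directly by an assumed .3 SD, the shares are 22-23% and 48%.

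**How often would mediation be claimed?** This used 1,500 simulated trials per setting with n = 118 (70% of 168), a Monte Carlo 95% interval and no true craving effect.

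| g | b | Interval excludes 0, no direct M-PE effect on craving | Interval excludes 0, direct effect of −.3 SD on craving |
|---|---|---|---|
| 0 | .3 | 0.2% | 0.9% |
| 0 | .5 | 0.3% | 2.1% |
| .3 | .3 | 1.7% | 12.4% |
| .3 | .5 | 4.7% | 25.1% |
| .5 | .3 | 11.7% | 30.9% |
| .5 | .5 | 24.1% | 68.8% |

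With g = .3 and no direct effect on craving, the estimate is biased but the false-claim rate stays below 5%. Above that it rises steeply.

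**Does the plan's other method help?** In the two-million runs, a marginal structural model weighted for post-randomisation PTSD gave a craving coefficient of at most 0.0024 in absolute value, against 0.08 to 0.23 unweighted. The true value was 0.

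**The case against.** The strongest reply is that the paragraph already holds the remedy. It promises several analyses of these pathways and names marginal structural models, which can handle a treatment-affected confounder. A reader might infer that these models are reserved for PTSD to use, so that the craving result rests on the GLMs alone. The text does not support that, since it gives the PTSD path priority without confining the models to it. What stands is that the models are not assigned to craving, and that running them alongside leaves the GLM estimate for craving biased.

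The PTSD-to-craving link is an assumption. This is right, and at g = 0 there is no bias. The size given here is therefore conditional.

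A reader might extend the point to cognitions. The documents do not support that. For cognitions and CAPS-5, PTSD severity is the outcome and cannot be the omitted confounder. For cognitions and use, PTSD may lie downstream of cognitions, and adjusting for it could remove a real indirect effect.

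The status of the analysis limits the stakes. The paragraph opens "Secondary exploratory analyses will assess gender as a potential moderator of treatment effects" and describes the mediating roles as potential. This stands, and it sets the weight of the point.

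Finally, the covariate list for the mediation models, and whether each mediator is modelled alone, are details that an article may leave to the analysis plan. Their absence is not criticised. The check takes craving as the only mediator in its models, which is one reading of the text.

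**Conclusion.** The point holds for one pathway, craving to substance use. There the GLM decomposition depends on a condition that the plan's own hypotheses put in doubt. If PTSD symptoms drive craving, with correlations of .3 to .6 and PTSD-use paths of .3 to .5 (assumed; not in the article), a craving effect that does not exist appears as about .016 to .104 SD. The share depends on the denominator: 9-36% if the whole effect on use runs through PTSD, about 3-18% if the total effect is the planned .58. Quoting only the larger range would overstate the case, because it is simply the squared PTSD-craving correlation.

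A reader might infer that the trial's main conclusions are at risk, or that craving is not a mediator. Neither follows. The between-group tests on CAPS-5 and TLFB do not use these models, and the check shows only that the GLM estimate cannot tell a craving mechanism from a marker of PTSD symptoms. This is a worthwhile, inexpensive improvement to an exploratory analysis.

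**What to change.** In section 2.8.2, or in the analysis plan:

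1. State that the marginal structural models also cover the craving-to-use pathway, with earlier post-randomisation PTSD severity as a time-varying confounder. The data are already collected: PCL-5 and craving during treatment (section 2.3.3), and CAPS-5, PCL-5 and craving at end of treatment and follow-up (Table 1).
2. Base any causal statement about craving on that analysis.
3. Present the GLM average causal mediation effect for craving on use as conditional on no treatment-affected confounding, and accompany it with a sensitivity analysis.

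The cost is wording and extra programming, and wider intervals for the craving effect. No new participants, visits or measures are needed. The trial is still running, so the change can be made before analysis.

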#### Qualitative analyses

2.8.3

Qualitative interviews will be analyzed using a rapid qualitative analysis framework [62,63]. The approach includes: 1) summarizing each interview using a template that will include separate areas for each main topic of inquiry and unexpected findings, 2) creating a data matrix that organizes the summary points for each main topic, 3) holding an analytic meeting for investigators and the interviewing team to provide their impression of the matrix contents, and 4) creating a final analytic memo summarizing the findings and noting key themes. Those summarizing interviews will conduct and discuss several summaries together to ensure consistency. Once consistency is achieved, remaining interviews will be coded by one study member with regular meetings to discuss emerging themes and questions.

## Discussion

3

PE has been demonstrated to be safe and effective among individuals with PTSD + SUD [[16], [17], [18]]. However, despite high rates of co-occurring PTSD + SUD [1,2] and evidence that PE is more effective for treating PTSD among those with PTSD + SUD than SUD treatment alone [12], PE is rarely available in substance-use treatment settings. Potential barriers to inclusion of PE are low attendance and high dropout rates [16,64,65]. One way to increase attendance is to use a massed format wherein PE is offered 3 to 5 times per week as opposed to once weekly sessions (M-PE). Early support for M-PE has shown comparable treatment outcomes and lower dropout rates compared to weekly PE [23]. Further, M-PE aligns with a typical length of stay for individuals in residential or comprehensive outpatient SUD programs. This hybrid Type I randomized controlled trial aims to investigate whether the inclusion of M-PE enhances treatment outcomes among those in SUD care compared to trauma TAU and best practices from enhancing treatment implementation.

Strengths of the study include use of a mixed methods design to capture clinical outcomes and qualitative experiences of both providers and participants. This design allows for comparison of M-PE to TAU on key PTSD and SUD outcomes while also capturing varied experiences of study site staff and participants to enhance implementation and sustainability of incorporation of trauma-focused care in SUD programming. Additionally, this study aims to examine mediators and moderators of treatment outcomes to further tailor PTSD + SUD intervention. Lastly, inclusion of individuals with subthreshold PTSD and the limited inclusion/exclusion criteria increases the generalizability of findings.

Despite these notable strengths, this study does have limitations. M-PE is designed to include 3-5 sessions per week. Though this structure works well in residential and comprehensive outpatient settings, it may be less feasible for those in outpatient SUD settings. Further, the limited inclusion/exclusion criteria is meant to enhance generalizability but also introduces potential confounds associated with co-morbid diagnoses (e.g., depression, anxiety, medical comorbidities) common in PTSD + SUD populations [66,67]. We also allow participants to engage in ongoing treatments for physical and mental health conditions which may confound treatment outcomes. Lastly, we anticipate we may see difficulties with attendance and treatment continuation as participants transition from residential to outpatient care. To address this, we have included frequent reminder calls from study staff regarding appointments, flexible treatment scheduling and assessment date ranges, and options for study-funded transportation (e.g., bus vouchers, ride shares).

There is strong empirical support for including trauma-focused interventions, such as PE, into SUD care [1,2,12]. M-PE has shown increased treatment attendance, decreased dropout, and comparable treatment outcomes to weekly PE [23,[29], [30], [31]]. This massed format may better fit the structure of residential and comprehensive outpatient SUD programming as the massed format allows for treatment completion within 3-5 weeks. This study will provide evidence as to whether the inclusion of M-PE to TAU in an SUD program enhances treatment and quality of life outcomes. Further, qualitative interviews will provide valuable information for the implementation and feasibility of M-PE in SUD care from the perspective of participants, providers, and administrators.

